#### Secondary outcome definition and measures

2.7.2

Protein intake on Day 7, defined as the actual protein delivered on study Day 7 (g/kg/day). For patients with BMI > 30 kg/m^2^, an AdjBW will be used.Occurrence of FI between ICU days 4–7, FI is defined as (6) present if any of the following criteria are met: ① Vomiting: any visible regurgitation of gastric contents, irrespective of volume. ② High gastric residual volume (GRV): any single GRV > 200 mL. ③ Diarrhea: ≥3 loose or liquid stools per day and stool weight >200–250 g/day or volume >250 mL/day. ④ Gastrointestinal (GI) bleeding: any intraluminal GI bleeding confirmed by gross blood in vomitus, gastric aspirate, or stool. ⑤ Insufficient enteral energy delivery: failure to achieve ≥20 kcal/kg body weight/day via the enteral route within 72 h after initiation/attempt of enteral feeding. ⑥ Cessation of enteral nutrition: enteral feeding discontinued for any clinical reason. Outcome recording. The presence or absence of FI will be assessed once per day on ICU days 4–7. In addition to the composite FI outcome, individual FI components will be reported and analyzed separately.Change in nutritional biomarkers. Defined as serum albumin and prealbumin concentrations measured on study day 1 (baseline) and day 7. Reporting values (albumin in g/L; prealbumin in mg/L) at each time point; change calculated as Day 7 − Day 1.Skeletal muscle status. Muscle mass change will be assessed using the following sonographic metrics on ICU days 1, 4, and 7 after admission: upper-limb muscle thickness; quadriceps muscle thickness; rectus femoris cross-sectional area (RF-CSA).Intestinal injury biomarkers. Between-group differences in intestinal injury markers will be evaluated using serum/plasma concentrations of D-lactate, intestinal fatty-acid binding protein (I-FABP), and diamine oxidase (DAO) on study Day 1 and Day 7. *Measurement & reporting:* assays performed per manufacturer instructions; values reported in assay-specified units. Changes from baseline (Day 7–Day 1) and between-group differences in change will be analyzed.New infections in the ICU: Defined as infections newly acquired ≥48 h after ICU admission.ICU length of stay.Ventilator-free days: Ventilator-free days within 28 days in the ICU.ICU hospitalization cost. Defined as the total direct medical cost accrued during the index ICU stay, from ICU admission (time 0) to ICU discharge. Extracted from the hospital billing system/financial data warehouse using patient identifiers and ICU encounter numbers.28-day mortality: Assessed on day 28 after ICU admission.90-day mortality: Assessed on day 90 after ICU admission.

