#### Data analysis

2.8.2

All statistical analyses will be conducted in accordance with a pre-specified statistical analysis plan. The primary analysis will follow the intention-to-treat (ITT) principle The Full Analysis Set (FAS) will include all participants who were successfully randomized and entered the intervention period, provided that they have a valid assessment of the primary outcome (caloric intake on day 7) or sufficient information to derive this value. The Per Protocol Set (PPS) will be a subset of the FAS, including participants who received the allocated intervention for at least 72 h and had no major protocol deviations. The PPS will be used for sensitivity analyses to assess the robustness of the primary findings. The SS will include all participants who received at least one dose of the study intervention and will be used for safety analyses.

The primary outcome, caloric intake on day 7 (continuous variable), will be analyzed using a linear regression model. The model will include the intervention group and the predefined covariates (APACHE II score, BMI, AGI grade, and primary diagnosis) as fixed effects. As this is a single-center randomized controlled trial, no random effects will be specified. To account for potential model misspecification and heteroscedasticity, heteroskedasticity-robust (sandwich) standard errors will be used for statistical inference. If the model residuals show substantial deviation from normality or are influenced by outliers, data transformation (for example, logarithmic transformation) or a nonparametric bootstrap method will be applied in sensitivity analyses to assess the robustness of the results.

Continuous secondary outcomes (e.g., the number of days without a ventilator in the ICU) will be analyzed analogously using linear regression models; secondary binary outcomes (e.g., FI) will be analyzed using a generalized linear model (GLM) with a logit link function. The model will include the intervention group and the pre-specified covariates as fixed effects. As this is a single-center study without inter-center or clustering structures, no random effects will be specified. In addition, because FI is a composite secondary endpoint, each FI component will be reported and analyzed separately alongside the composite FI outcome.

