Continuous variables will be summarized as mean ± SD if normally distributed, or as median and interquartile range (IQR, P25–P75) if not normally distributed. Between-group differences in continuous variables will be tested using the independent samples t-test for normally distributed data or the Mann–Whitney U test for non-normally distributed data. Categorical variables will be compared using the Chi-square test.

To assess whether between-group differences in caloric adequacy and tolerance reflect intrinsic physiological effects of the enteral formulas or are confounded by differences in feeding tolerance management, we will compare key nutrition-support process indicators (time to EN initiation; FIS-guided feeding-rate adjustments every 4–6 h; use of prokinetic and/or anti-diarrheal agents; post-pyloric feeding) between groups during the intervention period and will add these as covariates for adjusting confounding factors. At the same time, we will conduct sensitivity analyses to test the robustness of the results.

Sensitivity analyses will include: (I) an unadjusted GLM including only the treatment factor; (II) a covariate-augmented GLM including the prespecified covariates APACHE II score, AGI grade, BMI, primary diagnosis as well as baseline mechanical ventilation. (III) Key treatment indicators include time to initiation of enteral nutrition, feeding-rate adjustments at 4–6-h intervals based on the FIS score, use of prokinetics or antidiarrheals, and use of post-pyloric feeding. All covariates are prespecified and will be retained in the models regardless of statistical significance.

Adjusted odds ratios (ORs) with 95% confidence intervals (CIs) will be reported for binary outcomes, with standardized marginal risk differences provided as supplementary estimates. The primary endpoint will be tested at a two-sided *α* = 0.05 level without multiplicity adjustment. For prespecified secondary clinical endpoints, the false discovery rate (FDR) will be controlled at q = 0.05 using the Benjamini–Hochberg procedure based on two-sided *p* values from the specified models.

Process outcomes (such as fidelity, exposure, and contamination) will be treated as exploratory outcomes and summarized descriptively with 95% CIs; no hypothesis testing or multiplicity correction will be applied to these exploratory analyses.

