This study has several notable strengths. 1. To our knowledge, this is the first large randomized controlled trial to address whether, in critically ill patients with AGI whose intestinal function has recovered or at least not worsened, a transition from a PBF to an SPF is necessary. 2. We selected actual caloric intake as the primary endpoint to directly capture the impact of formula type on achieved nutrition, and we complemented this with a broad set of secondary outcomes—including actual protein intake, feeding tolerance, nutritional serum biomarkers, intestinal injury markers, trajectories of muscle mass, and key clinical endpoints—to provide a comprehensive and systematic evaluation. 3. Conducting the trial at a single center is expected to enhance consistency in the feeding protocol and ultrasound measurements. 4. To reduce heterogeneity and confounding, we excluded patients with hepatic or renal disease and those receiving extracorporeal therapies, conditions known to influence metabolism and nutritional requirements (23). 5. Moreover, clinical data are collected by an independent research team that is not involved in patient care, randomization, or data analysis, thereby minimizing subjective bias.

This study also has important limitations. 1. The single-center design may limit external validity and generalizability. 2. Our primary endpoint—caloric intake on ICU Day 7—introduces a risk of missing data among patients who are discharged or die before Day 7; these cases require imputation, which may deviate from true values. 3. Despite standardized training based on the guideline, some team-level subjectivity in implementation is unavoidable and could affect delivered feeding volumes or tolerance management. Although we will adjust for prespecified covariates, co-interventions and variability in feeding strategies may still influence the results, and residual confounding cannot be excluded. Our findings will be interpreted cautiously. 4. Finally, due to resource constraints, indirect calorimetry was not used to set energy targets, which may reduce the precision of prescribed goals.

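### Ventilator-free days accrue only in the ICU and give death no value, so early recovery can score below a long ICU stay or a death after extubation

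*Protocol article*

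**What the plan says.** Section 2.7.2 of the protocol article (Secondary outcome definition and measures) gives the whole definition in one line: "Ventilator-free days within 28 days in the ICU". Section 2.8.2 (Data analysis) uses the same outcome as its example for the linear model: "Continuous secondary outcomes (e.g., the number of days without a ventilator in the ICU) will be analyzed analogously using linear regression models". That restatement keeps the ICU restriction and does not repeat the 28-day limit.

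Mortality is a separate outcome, for example "28-day mortality: Assessed on day 28 after ICU admission", and is not linked to ventilator-free days. The Discussion recognises that the primary endpoint "introduces a risk of missing data among patients who are discharged or die before Day 7". The missing-data section deals only with day-7 caloric intake.

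For secondary clinical endpoints, the false discovery rate is controlled at q = 0.05 "using the Benjamini–Hochberg procedure based on two-sided *p* values from the specified models". The Discussion lists ventilator-free time among the key clinical outcomes.

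**The concern.** A ventilator-free-days outcome is meant to be higher when patients do better. Limiting the count to the ICU breaks this, because leaving the ICU alive ends the accrual just as death does. A patient who improves quickly gets few days. A patient who is off the ventilator but stays in the ICU gets many. Someone who dies in the ICU some days after extubation keeps the days accrued before death.

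If one formula led to earlier ICU discharge, its arm could show fewer ventilator-free days and be reported as worse on a tested outcome. The damage is to the direction of the comparison, not only to its precision.

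**Working it through.** The article states no figure for this outcome, so there is nothing to reproduce. The check applies the written rule to constructed patient courses. The courses are assumptions chosen to show how the rule behaves; they are not data from the trial. Each is compatible with the design, since the patient is alive and in the ICU on day 4, when randomization takes place. Each assumes ventilation from ICU admission and no reintubation.

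Let v be the day on which ventilation ends and L the day on which the ICU stay ends, through discharge or death. Three scores are compared:

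- As written (off the ventilator, in the ICU, within 28 days): min(L, 28) − v.
- Looser reading (the ICU wording ignored, no rule for death): 28 − v.
- Proposed: 28 − v for patients alive at day 28, and 0 for death by day 28.

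| Course | As written | Looser reading | Proposed |
|---|---|---|---|
| A. Extubated day 5, left ICU alive day 6 | 6 − 5 = 1 | 28 − 5 = 23 | 23 |
| B. Extubated day 5, still in ICU day 28 | 28 − 5 = 23 | 28 − 5 = 23 | 23 |
| C. Extubated day 4, died in ICU day 10 | 10 − 4 = 6 | 28 − 4 = 24 | 0 |
| D. Ventilated until death on day 6 | 6 − 6 = 0 | 28 − 6 = 22 | 0 |
| E. Ventilated 20 days, left ICU alive day 25 | 25 − 20 = 5 | 28 − 20 = 8 | 8 |

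The score as written orders the courses B (23), C (6), E (5), A (1), D (0). The quickest recovery, A, falls below a death (C) and below a patient ventilated for 20 days (E). A and B spent the same time on the ventilator and differ by 22 days only because B stayed in the ICU.

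The formula shows why. For stays up to 28 days, the written score rises by one for each extra ICU day and falls by one for each extra ventilator day. Suppose extubation and discharge both come one day sooner, for example from days 5 and 8 to days 4 and 7. The score goes from 8 − 5 = 3 to 7 − 4 = 3, so the gain is invisible. Under the proposed score it goes from 28 − 5 = 23 to 28 − 4 = 24. If only discharge comes sooner, the written score falls.

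The looser reading removes the discharge problem but exposes the missing death rule. A ventilated death on day 6 scores 22, against 8 for a survivor ventilated for 20 days. Neither reading gives a sound ordering.

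**The case against.** The strongest objection is that a journal article condenses the plan. How deaths score is commonly left to the statistical analysis plan, which the article says exists and which is not shown. This stands in part. That death has no value is inferred from silence, and a plan may supply one. The ICU restriction is different, because it is stated text in two sections and nothing in the article overrides it. A death rule added elsewhere would not restore the days lost by patients discharged alive.

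Three stronger readings are tempting, and the documents do not support them.

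- A reader might infer that early death in general scores better on ventilator-free days. Under the in-ICU count, a patient ventilated until death scores 0 (course D). The advantage exists only for death after extubation (course C), or under the looser reading without a death rule.
- A reader might conclude that linear regression is wrong here because the scores pile up near the maximum. Such a pile-up does not follow from the in-ICU count, where a high score needs a long ICU stay off the ventilator. The secondary analyses are modelled on the primary one, which uses heteroskedasticity-robust standard errors. A mean difference in days is a defensible estimand. Those standard errors, and the general rule of "independent samples t-test for normally distributed data or the Mann–Whitney U test for non-normally distributed data", deal with the shape of the distribution and not with how the score is built.
- A reader might say that "ICU length of stay" is misdefined because death shortens it. It is reported beside 28-day and 90-day mortality, where an excess of deaths would be visible. Replacing it would be a design preference.

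It is also fair to say that the courses are selected and do not show how often such patterns will occur.

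**Conclusion.** The point holds for the definition of ventilator-free days. Followed as written, early recovery scores 1 day where a long ICU stay scores 23 and a death after extubation scores 6, so the direction of benefit can reverse.

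This rests on taking the ICU wording literally in both sections, on no death rule existing in a document not shown, and on ventilator-free days belonging to the FDR-controlled family, which its place among the key clinical outcomes supports. The shift in the between-arm comparison cannot be computed, because the article gives no distribution of ICU stay or ventilation. It would depend on how far the formulas differ in time to ICU discharge.

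The outcome is secondary, and the primary analysis and the sample size are untouched. The definition should nevertheless be changed, because the present one cannot be relied on to point the right way.

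**What to change.** In section 2.7.2, define the outcome as the number of days alive and free of mechanical ventilation from ICU admission to day 28, regardless of location, with patients who die by day 28 scored 0. Use the same definition in the section 2.8.2 example. The planned linear model can stay. A rank-based or ordinal analysis may be added as a sensitivity analysis, and ICU length of stay may also be reported in survivors beside mortality; both are optional.

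The cost is a short amendment to an outcome definition, best dated before any comparison by arm. Day-28 vital status is already collected and follow-up runs to day 90, so the death rule needs no new data. The small downside is that ventilation after ICU discharge must be taken from the hospital record or assumed absent. The article does not say that it is collected, so the choice should be written down. It matters most for patients who leave the ICU still ventilated or are transferred. No sample size changes.

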### Study interventions

2.6

Following enrollment, all patients will receive a PBF during the run-in phase (study days 1–3). On study day 4, gastrointestinal function will be reassessed. Participants meeting AGI grade 0–I criteria are randomized (1:1) to one of two intervention arms: continuous Peptide-Based Enteral Formula Group (PBF group) and Sequential Standard Polymeric Enteral Formula Group (SPF group). All other aspects of ICU care follow contemporary best practice and local guidelines. Table 1 shows the schedule of enrolment, interventions, and assessments based on the SPIRIT 2013 statement (14). Detailed reporting checklists are provided in the Supplementary Table S2 (SPIRIT 2013 checklist).

**Table 1 tab1:** Schedule of enrolment, interventions, and assessments.

[figure not shown]

PBF group, Continuous Peptide-Based Enteral Formula Group; SPF group, Sequential Standard Polymeric Enteral Formula Group.

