#### General management

2.6.3

All other aspects of patient management will follow standard clinical practice. This includes, but is not limited to, monitoring of vital signs, feeding tolerance, laboratory testing, fluid resuscitation, mechanical ventilation, and vasopressor support, as deemed necessary by the attending clinical team. No study-directed interventions will be applied to any domain of care other than nutritional support. All concomitant treatments will be determined by the responsible clinicians and documented in the medical record.

Nutrition protocol. Enteral nutrition will be delivered in accordance with the 2019 European Society for Clinical Nutrition and Metabolism (ESPEN) guidelines (15). Because indirect calorimetry is not used in this study, the energy target will be set using a simplistic weight-based equation of 25–30 kcal/kg/day consistent with the 2016 ASPEN guideline (12) and several large clinical studies (17, 18), The protein target is 1.3 g/kg/day (15). For patients with obesity Body Mass Index (BMI) ≥ 30 kg/m^2^, adjusted body weight (AdjBW) will be used for energy and protein calculations, as recommended by 2019ESPEN guidelines (15). AdjBW = Ideal Body Weight (IBW) + 0.33 × (Actual Body Weight − IBW), where IBW is estimated using a BMI-based method [IBW = 2.2 × BMI + 3.5 × BMI × (height – 1.5 m)].

Food intolerance (FI) will be defined in accordance with the terminology and definition framework proposed by the ESICM (6) Working Group on Abdominal Problems in 2012. FI management in both groups will be conducted in accordance with the recommendations of the 2022 Evidence-Driven Feeding Guidelines for Nutrition in Critically Ill Patients (NEED) (17).

Parenteral nutrition (PN). In patients who do not tolerate full-dose enteral nutrition during the first week in the ICU, the safety and potential benefits of PN will be assessed case-by-case, with the final decision made by the attending physician.

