##### Exposure metrics

2.7.5.1

All participants receive a short-peptide formula from enrollment through study Day 3; this run-in period is not included in exposure analyses and is used solely for baseline standardization and tolerance assessment. Randomization occurs on Day 4 (D4). The exposure assessment window is D4–D7. We will record:

Duration of the exposure window (hours): elapsed time from randomization (D4) to 23:59 on D7 or to ICU transfer/discharge or death, whichever occurs first.Concordant feeding hours: cumulative hours during which the randomized formulation was actually administered.Adherence (%) = (concordant feeding hours ÷ exposure window hours) × 100. Interruptions (e.g., procedures, intolerance) will be time-stamped; calculations use actual accrued hours within the window.

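### ICU cost includes spending from before Day-4 randomisation, and the planned model does not adjust for it, so one secondary outcome loses precision that could be kept

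*Protocol article*

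**What the plan says.** Section 2.7.2 of the protocol article lists ICU hospitalisation cost as a secondary outcome: "Defined as the total direct medical cost accrued during the index ICU stay, from ICU admission (time 0) to ICU discharge". The figures come from the hospital billing system.

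Sections 2.4, 2.6 and 2.7.5.1 give every enrolled patient a peptide-based formula on study days 1–3 and place randomisation on Day 4. Section 2.7.5.1 says of those first days that "this run-in period is not included in exposure analyses and is used solely for baseline standardization and tolerance assessment".

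Only the type of formula is common to all patients in the run-in. For the rest of care, section 2.6.3 says: "All concomitant treatments will be determined by the responsible clinicians and documented in the medical record".

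Section 2.8.2 says that continuous secondary outcomes "will be analyzed analogously using linear regression models", and of the model terms: "The model will include the intervention group and the pre-specified covariates as fixed effects". The covariates named there are APACHE II score, BMI, AGI grade and primary diagnosis. A sensitivity model adds baseline mechanical ventilation, and another set adds feeding-process indicators. None of these is a cost measure.

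**The concern.** A between-arm outcome should, as far as possible, measure what allocation can change. Here the cost clock starts about three days before the arms diverge. It may start earlier still for some patients, because feeding may begin 24–48 h after ICU admission and the text uses both study day and ICU day. What is spent in that time (admission work-up, resuscitation, first ventilator days) is settled before allocation. It differs between patients because their care differs.

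That spending therefore adds patient-to-patient spread unrelated to formula. The same information, used as a baseline covariate, would explain part of the spread in later cost. The plan leaves it in the outcome and out of the model. At stake is the width of the confidence interval for the cost difference, and hence the chance of detecting a real one.

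**Working it through.** **Inputs.** From the documents: the cost window (ICU admission to ICU discharge), randomisation on Day 4, a linear model and its four covariates. The documents give no cost mean, SD, correlation or ICU stay, and no power calculation for cost, so there is no stated figure to reproduce. Everything below is a range under assumptions.

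**Notation.** Total cost = pre + post, split at randomisation. Let r = SD(pre)/SD(post), and let ρ be the correlation of pre and post. Variances are expressed relative to Var(post).

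- Total cost, unadjusted for pre: V = 1 + r² + 2rρ.
- Post-randomisation cost, adjusted for pre: A = 1 − ρ².

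**Direction.** V = (1 − ρ²) + (r + ρ)² = A + (r + ρ)². The last term cannot be negative. Apart from one degree of freedom, the planned analysis is therefore never more precise than the adjusted one, whatever the sign of ρ. The identity also holds after the existing covariates are fitted, with residual SDs and the partial correlation in place of r and ρ.

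**Size, V/A, ignoring the existing covariates.**

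| r | ρ = 0 | ρ = 0.3 | ρ = 0.5 |
|---|---|---|---|
| 0.2 | 1.04/1 = 1.04 | 1.16/0.91 = 1.27 | 1.24/0.75 = 1.65 |
| 0.3 | 1.09/1 = 1.09 | 1.27/0.91 = 1.40 | 1.39/0.75 = 1.85 |
| 0.5 | 1.25/1 = 1.25 | 1.55/0.91 = 1.70 | 1.75/0.75 = 2.33 |

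**Negative correlation.** Take 3 pre-randomisation days, a mean of 7 post-randomisation days at equal daily cost, a post-randomisation CV of 1.0 and a pre-randomisation CV of 0.4. Then r = (0.4 × 3)/(1.0 × 7) = 0.171. With ρ = −0.3, V = 1 + 0.029 − 0.103 = 0.927, which is below 1: total cost is less variable than post-randomisation cost alone. The adjusted variance is lower still: A = 1 − 0.09 = 0.91, so V/A = 1.02.

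**Allowing for severity.** In an illustrative simulation (400,000 patients, lognormal daily cost and stay, 3–5 pre-randomisation days), r was 0.28 and ρ was 0.34. That gives V = 1 + 0.078 + 0.190 = 1.27. After adjustment for a severity covariate, total cost had 1.16 times the variance of post-randomisation cost, and 1.18 times that of post-randomisation cost also adjusted for pre. The latter is a standard error about 9% larger (√1.18 = 1.09).

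**Choice of outcome once pre is in the model.** Because total = pre + post, regressing total on group, covariates and pre raises the coefficient of pre by exactly 1 compared with regressing post. The treatment coefficient, residuals and robust standard error are the same. In the untransformed linear model the start of the window then no longer matters.

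**The case against.** The outcome is fully defined, and the whole ICU bill is a legitimate quantity. ICU admission is also the anchor for mortality, treatment duration and follow-up. Cost is one of about eleven secondary outcomes and carries no power claim. All of this stands, and it limits the priority. It does not explain why a cheap and strongly related baseline value is left out.

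The covariate might be left to the analysis plan, which is not shown. But the article does not leave the model open: it names the covariates and says they are retained regardless of significance. If the full plan already adds pre-randomisation cost, the point is met.

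Several stronger readings are tempting and not supported:

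- **Bias.** Randomisation balances pre-randomisation cost in expectation, so the absolute difference is unbiased. Chance imbalance is part of the sampling error that the standard error already reflects.
- **Dilution of the effect.** If 30% of the bill precedes randomisation, a 10% saving in later cost appears as 10% × 0.70 = 7% of the total. The arithmetic is right, but the planned linear model estimates an absolute difference, which this does not alter. No percentage or ratio is specified for cost.
- **Identical care in the run-in.** Only the formula type is shared. If spending were truly identical, it would be a constant and add no variance.
- **A severe loss of information.** The ratio 2.33 would mean that 496 patients carry the information of about 213 (496/2.33). That is the extreme corner of the grid. It multiplies the window effect (1.75) by the ordinary gain from a baseline covariate (1/0.75), and it ignores the covariates already planned.
- **A contradiction with the exposure rules.** Section 2.7.5.1 leaves the run-in out because adherence to a randomised formula cannot exist before randomisation. It sets no rule for cost.

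**Conclusion.** The point holds as one of precision. Spending that allocation cannot affect is inside the ICU cost outcome, and the planned model does not adjust for it. Adjusting for it cannot make the estimate less precise, apart from one degree of freedom. The estimate as planned is unbiased.

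The size cannot be derived from the documents. Under SD ratios of 0.2–0.5 and correlations of 0–0.5, the variance ratio is 1.04 to 2.33 before the existing covariates are counted. The simulation with a severity covariate suggests 16–18%. With a negative correlation the gain may be close to nil. This is a modest, avoidable loss in one secondary outcome, of optional to moderate priority.

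**What to change.** In section 2.8.2, add ICU cost accrued before randomisation as a covariate in the linear model for ICU cost, taken by date from the same billing extract. Either total ICU cost or cost from randomisation to ICU discharge can then be the outcome, since both give the same treatment coefficient and standard error. If a percentage difference is quoted, also report post-randomisation cost, because the window does matter on that scale.

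The cost is one sentence in the plan and a date filter on the extract, assuming that billing lines are dated. No new patient measurement is needed and no care changes. The one small burden is a rule, written before the data are seen, for charges that fall on the day of randomisation.
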